#### Secondary outcomes

-Driving changes:

The secondary objectives focus on driving changes observed by the participants themselves, and changes in the participant observed by the caregiver (see Table 2). Several indicators will be used to obtain these measurements.

**Table 2 T2:** Measurements at baseline, 2 months and 6 months after the intervention on the patient and his caregiver.

**Outcome**	**Measure**	**Filled out by the:**		
		**Patient**	**Caregiver about the patient**	**Caregiver about himself**
Implementation of self-regulation strategies in driving	DPPQ's “Current Self-Regulatory Practices” (29)	x		
Indicators of driving changes	DHQ (30)	x		
Indicators of changes perceived by the caregiver	DHQ and DPPQ scales		x	
Indicators of driving ability self-awareness	Second part of the DHQ scale, objective measures from driving simulator and subjective measures from a questionnaire administered just after each simulator task.	x		
Indicators of mood effects of driving modifications	GDS (39)	x		x
Indicators of quality of life effect of driving modifications	QoL-AD scale (40)	x		x
Indicators of caregiver burden of driving modifications	ZBI (41)			x

Indicators of driving changes in participants will be measured at 2 months and 6 months by a composite score calculated using the first part of the Driving Habits Questionnaire (DHQ) (30) and the other DPPQ sub-scales. Indicators of driving changes perceived by the natural caregiver will be measured at 2 months and 6 months by a composite score which includes scores from the DPPQ and DHQ scales, and scores calculated from observations made by the caregivers about participants' driving. Indicators of self-awareness of driving ability will be measured at 2 months and 6 months by the score obtained in the second part of the DHQ scale filled out by the participant. Those questionnaires (DPPQ and DHQ scale) are self-reported measures but since the patient and the caregiver both answer about the patient driving, we may control for most of the bias induced by such measures. Moreover, authors such as Charlton et al. showed that results with objective methods about self-regulation of driving are coherent with self reported measures (24) which supports our use of those questionnaires.

-Driving performance and self-awareness of driving ability:

Driving performance and indicators of self-awareness of driving ability will be measured for participants who perform tasks on the driving simulator. Driving performance will be evaluated by 6 driving tasks, each of which will represent one scenario: (1) A speed maintenance task to measure the ability to respect a speed limit of 80 km/h and to maintain lane position; (2) A car-following task to measure the ability to keep the vehicle in lane while maintaining a safe distance; (3) an overtaking task to assess the ability to make correct decisions when overtaking a vehicle when driving on a high-speed road; (4) Driving in a rural area to measure the capacity to adapt to different road situations such as stop signs; (5) Driving in an urban area to evaluate the ability to adapt when driving in town, i.e. responding to traffic lights and adapting to unexpected events such as pedestrians crossing, a vehicle pulling out of a parking space suddenly; (6) A braking task to measure the ability to brake quickly. These tasks were designed to assess driving performance in different situations varying in difficulty. That is why we used a variety of driving situations often encountered while driving: high-speed road, rural area and an urban area. Moreover, the variety of the tasks [following a vehicle (1), respect speed limit and maintain lane position (2), overtaking (3), adapt to different road situations and unexpected events (4, 5) and braking (6)] assess different abilities (e.g., motor, attentional) required for driving and are frequently used in driving simulator studies (42–44). To avoid fatigue effects, the driving tasks are short (no longer than 5 min).

For each task, means and standard deviations of speed, lane position, steering angle, reaction times to traffic lights or unexpected events will be measured. In addition to the objective measures obtained from simulator data, subjective measures will be collected from a questionnaire administered to the participant immediately after each simulator task. While the participant will perform the driving task, the experimenter will fill out the same questionnaire about participant's driving ability (i.e., perception of participant's driving ability). The comparison between the scores obtained from the participant and the experimenter will inform on the participant's driving ability self-awareness. Finally, objective as well as subjective measures will inform on the participant's driving ability and his/her self-awareness of this ability, respectively.

- Mood:

Indicators of mood effects on driving modifications will be measured by the Geriatric Depression Scale 15-item version (GDS 15) (39) in both participants and their natural caregivers at 2 and 6 months.

- Quality of life:

Indicators of quality of life following driving changes will be measured by the Quality of Life in Alzheimer's Disease Scale (QoL-AD) (40) in both participants and their natural caregivers at 2 and 6 months.

-Caregiver burden:

Indicators of caregiver burden following driving changes by the participant will be measured 2 and 6 months by the Zarit Burden Inventory (ZBI) (41) for natural caregivers.

### Sample size and data analyses

The self-regulation strategy in driving will be considered beneficial if the score of “Self-Regulatory Practice” increases on average by two points (24) 2 months from inclusion. The number of subjects was computed by considering a Student *t*-test for equal variances between the two groups, with a two-sided alpha risk of 5% and a power of 80%. Based on the sample size calculation, 90 participants per group is considered sufficient to detect differences between the two assessments. Because a 10% loss of dyads is expected during the follow-up period, 100 participants per group will have to be recruited, i.e. a total of 200 participants.

Kolmogorov-Smirnov tests will be used to determine the normality of variables. For demographic, clinical, neuropsychological variables, and scores obtained from scales (e.g., the DPPQ), between-group differences will be examined using Fisher's Exact tests, independent Student *t*-tests or Wilcoxon rank-sum tests, as appropriate. The effect size in the intervention group compared to the control group will be quantified by estimating the difference in mean scores between the 2 groups (experimental vs. control) with a 95% confidence interval. A multiple linear regression model will be performed with DPPQ “Current Self-Regulatory Practices” as the dependent variable, and the level of cognitive impairment at inclusion and other characteristics that may have an effect on the outcome criterion as factors. A mixed-effect linear regression model will also be computed with DHQ, GDS-15, Qol-AD and ZBI as dependents variables, and the group (experimental vs. control) and follow-up time (inclusion, 2 and 6 months) as independent variables. The interaction between the intervention group and the follow-up time will be observed.

The concordance between the performance on the driving simulator and the perception of driving ability measured immediately after simulated driving will be estimated by the Lin concordance correlation coefficient and by the Bland & Altman method for continuous criteria, and by the Cohen Kappa coefficient for ordinal criteria. The number of participants who significantly change their estimation at 2 and 6 months compared to before the intervention will be measured from objective and subjective measures at the different points in time.

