### Randomization

Randomization between the two groups will be stratified in the individual recruitment centers, based on participants' level of cognitive disorder (two levels: minor or major). Randomization by block permutation will be carried out in order to balance the two groups (experimental and control groups), and to allow the workshops to start in the experimental group, which requires a minimum of four dyads. The block permutations will differ in size to ensure the unpredictability of the random allocation.

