### Intervention description

#### Experimental group

Dyads included in the ACCOMPAGNE educational program group will take part in seven collective workshops, spread over three half-days (once a week for three consecutive weeks). Each workshop lasts approximately an hour and a half and uses educational content and pedagogical methods. Materials and methods of each workshop are described in Table 1.

**Table 1 T1:** ACCOMPAGNE program workshops.

**Workshop (duration)**	**Main objective and methods**	**Materials (example)**
Workshop introduction (1 h)	Main objective: To increase participant's involvement by considering him/her as a key member of the workshops and to initiate a group dynamic.	
	Method: Round table: each participant answers the questions on the “question wheel”: Name, first name, age, place of residence. Do you like to drive? Do you drive often? For which activities? Do you experience any difficulties when driving? Motor skills? Concentration? Memory problems?	
Cognitive skills workshop (1h30)	Main objective: to facilitate awareness of the cognitive skills involved in driving (visuo-spatial, attentional, memory, executive).	[figure not shown]
	Method: After defining the different cognitive mechanisms involved in driving, role plays are distributed. The participants have to imagine the cognitive mechanisms involved in each situation.	
Perception and environment workshop (1h30)	Main objective: To facilitate awareness of sensorimotor skills required to drive safely.	[figure not shown]
	Method: For each visual skill (acuity, accommodation, contrast and distance vision) the facilitator creates a discussion around the questions “What role does this skill play in driving? What is the risk if this skill is impaired?” Establishment of a checklist based on sensory status and level of alertness green light = safe driving/orange = adaptation required/red = do not drive	

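### The sample size and the named primary analyses treat dyads as independent although one arm is treated in workshop groups; if outcomes correlate within groups, power is overstated and the test is liberal

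*Protocol article*

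**What the plan says.** Delivery differs between the arms. Under Intervention description (Experimental group), the dyads "will take part in seven collective workshops, spread over three half-days (once a week for three consecutive weeks"). The Randomization section says that blocks are used partly "to allow the workshops to start in the experimental group, which requires a minimum of four dyads", and Procedure adds that delivery begins once four are available. No maximum is given. Under Control group, dyads receive the usual recommendations from their physician at a memory-clinic consultation.

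The section Sample size and data analyses uses a Student t-test "for equal variances between the two groups, with a two-sided alpha risk of 5% and a power of 80" per cent. Benefit is defined as a score that "increases on average by two points" at 2 months, and "90 participants per group is considered sufficient to detect differences between the two assessments". The only inflation is for attrition, put at one dyad in ten, which leads to the statement that "100 participants per group will have to be recruited, i.e. a total of 200 participants".

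For the scale scores, including the DPPQ, the section names independent t-tests or Wilcoxon rank-sum tests and a difference in means with a 95% interval. It adds a multiple linear regression for the primary subscale, whose factors are cognitive level and other characteristics. A mixed-effect model is named for DHQ, GDS-15, QoL-AD and ZBI, with arm and time as independent variables; its random effects are not described.

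**The concern.** This is a partially nested design: dyads are grouped after randomization in one arm and not by design in the other. Members of a workshop group share facilitators and sessions and work out solutions together. The strategies workshop covers night driving, rush hour, motorways and bad weather, and the primary subscale scores avoidance of much the same situations. Some within-group correlation is therefore plausible.

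If it exists, the mean of the experimental arm varies more than a t-test for independent dyads assumes. The standard error of the arm difference is then too small, the interval too narrow and the stated power too high. The error runs in the same direction for any positive ICC.

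**Working it through.** **Inputs from the protocol article:** difference 2 points; two-sided alpha 5%; power 80%; 90 analysable per arm; 10% loss; minimum workshop group of 4 dyads.

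**Assumptions, not in the document:** ICC of 0.02, 0.05 or 0.10; mean group size m of 4 (the stated minimum) or 8 (illustrative); equal total variance in both arms; no correlation among controls.

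**1. The plan's own figures.** No standard deviation is stated, so 90 per arm cannot be reproduced directly. Solving for the SD that makes it correct with independent dyads:

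SD = 2 × √(90/2) / (1.960 + 0.842) = 4.79, a standardised difference of about 0.42. The noncentral t gives 4.76.

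The attrition step reproduces: 90 / (1 − 0.10) = 100. The step from 90 to 100 therefore contains no design effect.

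**2. Standard error with grouping in one arm.**

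DE = 1 + (m − 1) × ICC, in the experimental arm only

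SE = SD × √(1/90 + DE/90), so the ratio to the independent-dyad SE is r = √((1 + DE)/2)

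Power of a valid test = Φ(2.80/r − 1.96)

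Type I error of the planned test = 2 × (1 − Φ(1.96/r))

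**3. One case in full: m = 4, ICC = 0.05.** DE = 1 + 3 × 0.05 = 1.15; r = √(2.15/2) = 1.037. Power = Φ(2.80/1.037 − 1.96) = Φ(0.74) = 77%. Type I error = 2 × (1 − Φ(1.89)) = 5.9%.

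**4. Range.**

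| m | ICC | DE | Power, valid test | Type I error, planned test | Recruits per arm for 80% |
|---|---|---|---|---|---|
| any | 0 | 1.00 | 80% | 5.0% | 100 |
| 4 | 0.02 | 1.06 | 79% | 5.4% | 103 |
| 4 | 0.05 | 1.15 | 77% | 5.9% | 108 |
| 4 | 0.10 | 1.30 | 74% | 6.8% | 115 |
| 8 | 0.02 | 1.14 | 77% | 5.8% | 107 |
| 8 | 0.05 | 1.35 | 73% | 7.1% | 118 |
| 8 | 0.10 | 1.70 | 67% | 9.2% | 135 |

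A simulation of the planned t-test (40,000 runs per setting, SD 4.79) gave type I error of 5.8% and 6.6% for groups of 4 at ICC 0.05 and 0.10, and 7.1% and 9.0% for groups of 8. This agrees with the formula.

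**5. Interval width.** The correct 95% interval is wider by the factor r: about 4% at m = 4, ICC 0.05, and 16% at m = 8, ICC 0.10 (r = √(2.70/2) = 1.162).

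**The case against.** The strongest reply is that the harm depends on quantities that the document does not give. At ICC 0 nothing changes. Content is standardised, facilitators must be trained and experienced, the strategies workshop is adapted to each dyad, and the outcome is the driver's own reported practice. All this may keep the ICC low. Since delivery starts at four dyads, groups may often be near that size; groups of 8 are possible but undocumented. The regression on participant characteristics may also recover some precision. These points stand. They limit the size of the problem, but they do not justify an ICC of exactly zero.

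The type I error figures also need a qualification. If the program affected nobody, attending a workshop would create no correlation, and likeness due to centre or recruitment period is not specific to one arm. The inflation applies when group effects differ but average to zero. The points on power and interval width remain when the program works to a varying degree.

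Controls at a centre may share a physician, so correlation confined to one arm is a simplification.

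A reader might infer that every planned analysis ignores the grouping. The article does not show that. The random effects of the mixed model for the secondary scales are not described, and an article may leave them to the full protocol or the SAP.

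**Conclusion.** The point holds for the sample size and for the analyses named for the primary DPPQ outcome. Both treat dyads as independent while one arm is treated in groups of at least four.

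It is conditional on a positive ICC. At the documented minimum group size the effect is modest: 1 to 6 points of power and 0.4 to 1.8 points of type I error for ICC 0.02 to 0.10. It becomes material with larger groups, where power could fall to about 67% and type I error reach about 9%. All power figures start from the stated 80%, which cannot itself be checked without an SD.

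It is tempting to conclude that the stated 80% and 5% simply do not hold. The document supports only that they hold if dyads in the same workshop group are uncorrelated, an assumption that is neither stated nor likely to be exactly true. This should be corrected, but it does not invalidate the trial.

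**What to change.** - Record a workshop-group identifier for every experimental dyad during delivery; membership may be hard to reconstruct later.
- Analyse the DPPQ subscale with a partially nested mixed model: a random effect for workshop group in the experimental arm, each control dyad as its own cluster, and small-sample degrees of freedom. The last matters because 90 dyads make only about 22 groups of 4 (90/4 = 22.5) or 11 groups of 8 (90/8 = 11.25).
- Include the same random effect in the mixed models already planned for DHQ, GDS-15, QoL-AD and ZBI.
- Restate the power for 90 per arm under a declared ICC and group size; for example, about 77% at ICC 0.05 with groups of 4, before any gain from covariate adjustment.

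The cost is one recorded variable, some analysis wording, a slightly wider interval and a slightly lower stated power. No added participants are required; the recruitment figures in the table show what holding 80% would take.

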### Outcomes and assessment tools

#### Main outcome: Implementation of self-regulation strategies

The main outcome is the implementation of self-regulation strategies in driving. Self-regulation strategies will be measured by the participants' scores on the DPPQ “Current Self-Regulatory Practices” subscale (29). The 2-month and 6-month scores of the control group and the experimental group will be compared. The subscale includes eight questions about the frequency of drivers' self-regulation strategies. These strategies consist of: waiting for the rain to stop before driving; asking someone to accompany them rather than driving alone; looking for parking lots to avoid parallel parking; avoiding turning left in traffic; avoiding taking the freeway; avoiding rush-hour traffic; avoiding driving in crowded places; and avoiding driving at night. A four-point scale (0: never, 1: rarely, 2: sometimes, 3: often) reflects the frequency of each item, creating a total score ranging from 0 (never uses any of these strategies) to 24 (uses all strategies often).

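### The stated primary effect is an unadjusted difference in DPPQ scores, and no analysis of that outcome names the baseline DPPQ already collected; naming it as a covariate would raise power at almost no cost

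*Protocol article*

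**What the plan says.** All references are to the protocol article.

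- **Primary comparison** (Main outcome section): "The 2-month and 6-month scores of the control group and the experimental group will be compared".
- **Effect measure** (Sample size and data analyses): the effect is to be "quantified by estimating the difference in mean scores between the 2 groups (experimental vs. control) with a 95% confidence interval". No covariate is attached to this estimate.
- **Choice of test** (same section): "Kolmogorov-Smirnov tests will be used to determine the normality of variables". Scale scores, with the DPPQ as the example, are then compared by a t-test or a Wilcoxon rank-sum test, whichever is judged suitable.
- **Regression on the primary outcome** (same section): a multiple linear regression with the DPPQ subscale as dependent variable. The only factor named is the level of cognitive impairment at inclusion; the rest are unspecified characteristics that might influence the outcome. Treatment group, baseline DPPQ and the time point are not named.
- **Mixed model** (same section): "A mixed-effect linear regression model will also be computed with DHQ, GDS-15, Qol-AD and ZBI as dependents variables", with group, time (inclusion, 2 and 6 months) and their interaction. The primary DPPQ subscale is not listed.
- **Baseline data** (Procedure): the neuropsychologist administers the DPPQ to the participant on the day of inclusion, and again at 2 and 6 months.
- **Sample size** (Sample size and data analyses): a benefit is a score that "increases on average by two points (24) 2 months from inclusion"; the calculation uses a two-group t-test "with a two-sided alpha risk of 5% and a power of 80" per cent; "90 participants per group is considered sufficient to detect differences between the two assessments"; and, after 10% loss, "100 participants per group will have to be recruited, i.e. a total of 200 participants".

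**The concern.** In a trial with a continuous primary outcome measured on the same scale before randomised treatment, the baseline value is usually the strongest available predictor of the follow-up value. Leaving it out of the primary estimate leaves explainable variance in the error term. The interval is then wider and power lower than the collected data allow.

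Here the trial would gather the baseline value, use the inclusion value of the secondary scales in a longitudinal model, and report the primary effect without it. The article itself warns, under Potential pitfalls and unintended effects, that recruitment may fall short, so avoidable loss of precision on the primary question matters.

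There is a smaller, related point. If the normality test leads to a Wilcoxon test, the p-value comes from a rank comparison while the reported effect is still a difference in means with its interval. The two no longer belong to the same analysis.

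**Working it through.** **Inputs**

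- From Sample size and data analyses: difference 2 points, two-sided alpha 5%, power 80%, 90 evaluable per arm, 10% loss.
- Not stated, back-solved: the SD.
- Not stated, assumed: the correlation r between baseline and 2-month DPPQ, taken as 0, 0.3, 0.5 and 0.7.

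**1. The plan's own figure**

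The 90 per arm cannot be reproduced independently, because no SD is given. Solving for it:

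SD = 2 × √(90/2) / (1.960 + 0.842) = 2 × 6.708 / 2.802 = 4.79.

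The noncentral t distribution gives 4.76. The loss allowance does reproduce: 90 / (1 − 0.10) = 100 per arm.

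**2. Unadjusted comparison of follow-up scores**

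SE = 4.79 × √(2/90) = 0.714. Signal-to-noise ratio = 2 / 0.714 = 2.80. Power = Φ(2.80 − 1.96) = 80%. The 95% interval half-width is 1.96 × 0.714 = 1.40 points.

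**3. Adjusted for baseline DPPQ**

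The residual SD is 4.79 × √(1 − r²); the other steps are as above.

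| r (assumed) | Residual SD | SE | 2/SE | Power at 90 per arm | 95% CI half-width | n per arm for 80% |
|---|---|---|---|---|---|---|
| 0 | 4.79 | 0.714 | 2.80 | 80.0% | 1.40 | 91 |
| 0.3 | 4.57 | 0.681 | 2.94 | 83.6% | 1.33 | 82 |
| 0.5 | 4.15 | 0.618 | 3.24 | 89.9% | 1.21 | 68 |
| 0.7 | 3.42 | 0.510 | 3.92 | 97.5% | 1.00 | 46 |

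The price of adjustment is one degree of freedom. At r = 0 the noncentral t gives 79.6% against the nominal 80.0%, so the worst-case loss is about 0.4 percentage points or less.

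**4. If change scores were meant**

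The SD of a change is 4.79 × √(2(1 − r)), taking 4.79 as the SD of a single score.

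- r = 0.3: SD 5.67, SE 0.845, power 66%.
- r = 0.5: SD 4.79, SE 0.714, power 80%.
- r = 0.7: SD 3.71, SE 0.553, power 95%.

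The variance difference between the two methods is proportional to 2(1 − r) − (1 − r²) = (1 − r)², which is never negative. Baseline adjustment is therefore at least as efficient as change scores at every r. This also holds if 4.79 is read as the SD of the change, since the ratio of the adjusted variance to the change-score variance is (1 + r)/2, at most 1.

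**5. Simulation check**

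Scores were rounded and bounded to 0–24, with 4,000 trials per scenario.

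| r | t-test | Test chosen by Kolmogorov-Smirnov | Baseline-adjusted |
|---|---|---|---|
| 0.3 | 80.0% | 80.0% | 83.3% |
| 0.5 | 79.7% | 79.7% | 89.9% |
| 0.7 | 79.8% | 79.8% | 97.1% |

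Type I error lay between 4.4% and 5.2% for every method. The normality test led to a Wilcoxon test in about 1% of trials.

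**The case against.** **An adjusted model of DPPQ is already planned.** This is the strongest reply. A reader might infer that the primary outcome gets no covariate adjustment at all, and the article does not support that. Its regression could take in baseline DPPQ among the unspecified characteristics, and a condensed article may leave the covariate list to a fuller document. What remains is narrower: the text that is shown names neither baseline DPPQ nor group in that model, and states the effect measure as the raw mean difference. As written, the regression does not yield a baseline-adjusted treatment effect.

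**The plan may mean change from baseline.** The sample-size text speaks of an increase from inclusion and of differences between two assessments, whereas the Main outcome section compares scores. If change was intended, baseline is already used and the 80% starting point holds only at r = 0.5 when 4.79 is the SD of a single score. The gain at r = 0.7 then shrinks from 17.5 points to about 2.5 (97.5% against 95%). This affects the size of the gain, not its direction.

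**The normality pre-test does little numerical harm.** This stands. One might infer that letting the data choose the test inflates type I error or costs power; the simulation shows neither in near-normal scenarios. The sentence on choosing tests is also generic, covering demographic and clinical variables, and the sample-size text ties the Student t-test to the primary outcome. Only the mismatch between a rank p-value and a mean difference remains.

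**The mixed model would recover few missing dyads.** This also stands. For the 2-month contrast, it gains follow-up information only from dyads that miss month 2 and attend month 6. Dyads lost for good contribute no later visit, so missing data are not a main argument for the change.

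**Conclusion.** The point holds as one of efficiency, not validity. Randomisation makes the unadjusted difference an unbiased estimate, and the trial is sized for it, so it would be wrong to call the planned comparison erroneous or biased. The shortfall is that a baseline value already collected is not named in any analysis of the primary outcome.

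At 90 per arm, naming it would raise power from 80% to about 84%, 90% or 97.5% for r of 0.3, 0.5 or 0.7. Relative to change scores the starting points would be about 66%, 80% and 95%. These figures rest on a back-solved SD and an assumed r; the article gives neither. That adjustment is at least as efficient as change scores does not depend on those values, and against raw scores it can lose no more than a fraction of a percentage point.

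The pre-test point is secondary and concerns coherence between p-value and estimate.

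**What to change.** Make the regression already planned for DPPQ the primary analysis, or extend the existing mixed model to DPPQ. Name its terms: group, baseline DPPQ and the randomisation stratification factors (centre and cognitive level). Take the 2-month arm difference, its 95% confidence interval and its p-value from that one model. State that the Kolmogorov-Smirnov test does not select the primary test, and keep the Wilcoxon rank-sum test as a sensitivity analysis. Align the sample-size wording so that it is clear whether the 2 points are a difference between arms in score or in change.

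The cost is analysis-plan wording only. No extra data, visits or participants are needed, and the planned 200 can stand.

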### Potential pitfalls and unintended effects

This study may face different difficulties. As it tackles the delicate question of driving among olders and more specifically among olders with neurocognitive disorders, we could face difficulties in recruiting participants. Indeed, it is possible that participants with neurocognitive disorders may not take part in this study due to a fear of license loss, even if there is no implication for reporting medically at-risk drivers to the jurisdiction's governing authority. Moreover, we need to include patient/caregiver dyads, thus, in order to be involved in the study, the patient will need to have a natural caregiver, available and willing to participate which reduces the number of potential participants. If recruitment difficulties turn out to be too important, it could lead to a small sample size, which may limit the generalisability of the results. In addition, uncontrolled intercurrent variables related to the individual history of the disease could bias our result. That is why, we choose to control for such variables as best as possible by using questionnaires about life events at 2 and 6 months. Furthermore, the intervention duration (i.e., 3 weeks) may not be sufficient to produce the expected outcomes. Lastly, for the subgroup of patients who undergo a driving task, the use of the driving simulator can generate simulator sickness and may frighten or shock the patient if he/she makes a serious mistake in the driving scenarios such as hitting a pedestrian or another car.

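### The planned group comparison on the DPPQ subscale ignores the randomisation strata and the baseline score, and the accompanying regression does not name randomised group or centre or restrict its covariates to baseline

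*Protocol article*

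**What the plan says.** **Allocation.** Under Randomization: "Randomization between the two groups will be stratified in the individual recruitment centers", with minor or major cognitive disorder as the second factor. The Design section gives four centres.

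**Group comparison.** Under Sample size and data analyses, scale scores including the DPPQ are compared by Student t-test or Wilcoxon rank-sum test. The effect is reported as a difference in group means with a 95% confidence interval. The sample size was obtained "by considering a Student *t*-test for equal variances between the two groups". No stratum and no baseline value enters any of these.

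**Regression.** The same section adds a multiple linear regression on the DPPQ subscale, with "the level of cognitive impairment at inclusion and other characteristics that may have an effect on the outcome criterion as factors". The next sentence, on the mixed model for DHQ, GDS-15, QoL-AD and ZBI, does name group and follow-up time.

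**Baseline score.** Under Procedure, the DPPQ is administered at the inclusion visit, so a baseline value will exist.

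**Life events.** Under Procedure, events between visits are asked about at 2 and 6 months. Under Potential pitfalls and unintended effects, the authors fear bias from intercurrent variables and so choose to "control for such variables as best as possible by using questionnaires about life events at 2 and 6 months".

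**The concern.** Stratified allocation removes between-stratum variation from the true sampling error of the group difference. An analysis that ignores the strata still charges for that variation, so its intervals are too wide and its test falls below the nominal 5%. Leaving out the baseline value of the same scale gives up further precision at no saving.

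The regression could have recovered this, but its wording does not secure it. It names one of the two stratification factors and leaves both group and centre unnamed. The timing at inclusion attaches only to cognitive level, so the open remainder of the list could admit variables measured after randomisation.

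That matters because of the life-event rationale. In a randomised comparison, later events that the programme does not affect add noise but do not bias the contrast. Events that it does affect are part of its effect, and conditioning on them can remove some of that effect. The stated reason for controlling them therefore points the wrong way.

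**Working it through.** **Inputs from the article (Sample size and data analyses)**
- Two-sided alpha 5%, power 80%.
- Target difference of 2 points: the score "increases on average by two points (24) 2 months from inclusion".
- 90 evaluable per group; 10% loss; 100 per group recruited.
- SD: not stated.

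**Step 1: the plan's own figures**
- Inflation: 90 / (1 − 0.10) = 100 per group. This reproduces.
- The 90 cannot be derived independently without an SD. Back-solving: SD = 2 / [(1.960 + 0.842) × √(2/90)] = 2 / (2.802 × 0.1491) ≈ 4.79. The t-test version gives 89.5 per group at SD 4.75 and 91.4 at SD 4.80, which agrees.
- Other SDs would have required 63 (SD 4), 99 (SD 5) or 142 (SD 6) per group. The power figures below therefore hold only for SD ≈ 4.79. The alpha and interval-width figures do not depend on the SD.

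**Step 2: strata ignored in the analysis**

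Let R² be the share of outcome variance explained by the strata (assumed), with groups balanced within strata and a normal approximation.
- The true standard error is √(1 − R²) times the one the unadjusted test uses.
- Effective critical value: c = 1.960 / √(1 − R²).
- Actual alpha = 2 × [1 − Φ(c)].
- Unadjusted power = Φ(2.802 / √(1 − R²) − c).
- Adjusted power = Φ(2.802 / √(1 − R²) − 1.960).
- Interval-width ratio, unadjusted to adjusted = 1 / √(1 − R²).

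| R² (assumed) | Actual alpha | Power, unadjusted | Power, adjusted | Width ratio |
|---|---|---|---|---|
| 1% | 0.049 | 80.1% | 80.4% | 1.005 |
| 5% | 0.044 | 80.6% | 82.0% | 1.026 |
| 10% | 0.039 | 81.3% | 84.0% | 1.054 |
| 20% | 0.028 | 82.7% | 87.9% | 1.118 |

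Worked row, 5%: √0.95 = 0.9747; c = 2.011; 2.802 / 0.9747 = 2.874; unadjusted Φ(0.863) = 80.6%; adjusted Φ(0.914) = 82.0%. The loss is 1.4 points at 5% and 2.7 points at 10%.

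**Step 3: baseline DPPQ**

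If the baseline score correlates r with the outcome, adjustment multiplies the residual variance by 1 − r². Allocation does not balance the baseline score, so on this account the unadjusted test stays at 80.0% power with nominal alpha. The adjusted-power formula above applies with r² in place of R²: r² = 10% gives 84.0% and r² = 20% gives 87.9%. The article gives no r, so these are illustrations only.

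**Step 4: life events, conditional illustration**

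Suppose they were entered as covariates, carried a share m of a true 2-point effect, and left residual variance unchanged. The estimate becomes 2 × (1 − m), and power = Φ(2.802 × (1 − m) − 1.960).
- m = 10%: 1.8 points, 71% power.
- m = 25%: 1.5 points, 56% power.
- m = 50%: 1.0 point, 29% power.

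No value of m can be taken from the article.

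**The case against.** The strongest reply is that this is a condensed article whose full analysis plan is not shown, and that covariate lists are normally settled there. Several stronger readings do fail on the text:

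- **That the regression omits centre.** It does not name centre, but the open phrase could include it.
- **That no programme effect is estimated.** The sentence before the regression gives the difference in means with a 95% interval. The unnamed group term leaves only the role of the regression unclear.
- **That ignoring the strata biases the result.** It does not; the test errs on the conservative side.
- **That it costs 2 or 4 points of power.** That sets the adjusted 82.0% or 84.0% against a fixed 80%. Balanced strata raise the unadjusted test's power too, so the fair gaps are 1.4 and 2.7 points. For the regression, which already names cognitive level, only centre's share is in question.
- **That life events will shrink the primary estimate.** They are mentioned in the limitations and procedure text, not in the analysis section. No model is named and the questionnaire items are not given. Prognostic events would also reduce residual variance, which Step 4 holds fixed.

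What survives is not a matter of missing detail. The unadjusted comparison is a stated method, and a better one is available from data already being collected. The secondary-outcome model shows that the authors name group when they choose to. The reason given for controlling post-randomisation events is itself unsound, wherever it would be applied.

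**Conclusion.** The point holds as one of efficiency and specification, not of a biased planned comparison. The stated group comparison uses neither stratum nor the baseline DPPQ score. For strata explaining 5% to 10% of the variance, this lowers alpha to about 0.044 to 0.039, widens the interval by about 3% to 5% and costs about 1.4 to 2.7 points of power. Those figures rest on the assumed variance shares and balanced strata, and the power figures also on the back-solved SD of about 4.79. The loss from leaving out the baseline score may be larger, but cannot be sized from the article.

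The life-event intention is a risk, not an established error. A reader might infer that the primary effect will be attenuated, for example from 2.0 to 1.5 points. That would require both that the events enter the primary model and that the programme changes them, and the article states neither.

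**What to change.** - Make the primary estimate the group coefficient, with its 95% confidence interval, from a linear model for the DPPQ subscale score with randomised group, baseline DPPQ, centre and cognitive level (minor or major).
- Limit any other covariates to a prespecified list measured before randomisation.
- Use life events only to describe the groups or in a sensitivity analysis labelled as such, and remove the suggestion that adjusting for them protects the comparison from bias.
- Keep the unadjusted mean difference as a supporting result if wanted.

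The cost is analysis-plan wording. Four centres take three degrees of freedom, and cognitive level and baseline DPPQ one each: five in all, leaving 180 − 7 = 173 residual degrees of freedom against 178 for the t-test on 180 evaluable participants. No new data are needed and the sample size need not change. If a full analysis plan already fixes these terms, it is enough to confirm that and align the article's wording.
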